### Data Management

The data collected from survey materials will be entered and stored electronically on a secure (password-protected) database system (REDCap^TM^) for the duration of the data collection and analysis (estimation one year), and only specified study coordinators/collaborators will have access to the surveys and monitor the data accordingly for research purposes only.

### Sample Size Estimation and Power Calculations

Power analysis for a priori sample size was performed with equivalence testing for two proportions in a randomized design using the program nQuery advisor. Using data on previous research, we estimated that 45% of patients receiving conventional CR, and 74% of patients attending *Destination Rehab* with conventional CR would have at least one correction of a cardiovascular behavioral risk factor at 12 months [29]. Therefore, to discover a clinically-relevant difference of this size between the groups at a 0.05 alpha level with 80% power, we will require 50 participants per group. Assuming a drop-out rate of 10%, we aim to recruit a total of 120 patients for the RCT.

### Statistical Analysis

#### Quantitative Data

For normally distributed variables, simple arithmetic means and standard deviations will be calculated. For categorical variables, frequencies and proportions will be calculated. For clinical endpoints, we plan to calculate changes in measures by comparing differences in change from baseline to follow-up interval. We will include sensitivity analyses with the inclusion of patients with complete data only. Analyses will be performed using commercial software (SAS version 9.2, SAS institute), and a two-tailed value of *P*<.05 as statistically significant.

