#### Baseline Visits

All participants will undergo an outpatient, baseline assessment for collection of sociodemographics, medical history, prescribed medications/adherence [39], smoking status, surveys for heart disease knowledge [40], diet quality [41,42], physical activity patterns [43,44], self-efficacy [41,44,45], social support/influence [46], and physical and mental health-related quality of life [47] utilizing validated instruments after obtainment of written informed consent. Clinical assessments including anthropometrics (height, weight, body mass index, waist circumference, and blood pressure) and laboratory studies (lipid panel, blood glucose, and hemoglobin A1c) will be obtained by standard protocols and/or extracted from participant medical records from their ACS index hospitalization or follow-up medical visits. As a part of the standard clinical CR intake process, all participants will undergo an oxygen consumption exercise treadmill test (ETT) to assess for heart rate and blood pressure responses and exercise capacity. All participants will attend an in-person computer and device training session similar to that carried out during the feasibility study and will receive a personal laptop and headset for use during the study (both control and intervention groups for standardization). Participants will also receive a personal activity tracker (Fitbit^TM^ ) as a tool to accurately assess free-living physical activity [48]. Participants will be asked to wear the activity trackers on a daily basis and to upload their data to a secure webserver at least once weekly. Each participant will receive a binder of education materials (including slide presentations) relevant to their respective assignment.

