#### Measures

The primary outcome is a composite including improvement of at least one of the following 3 cardiac risk factors at baseline, 3, 6, and 12 months (1) physical activity (at least 150 minutes per week), (2) diet (consumption of five or more fruits and vegetables daily), and (3) smoking (complete cessation for baseline smokers, maintained nonsmoking status for baseline nonsmokers). Secondary outcomes will include improvement in all 3 cardiac risk factors, intention and self efficacy to achieving lifestyle change [41,44,45], change in exercise capacity by peak oxygen uptake (VO_2_), change in weight (≥5% weight reduction for patients with baseline BMI >30 kg/m^2^), blood pressure optimization (blood pressure <140/90 mmHg, <130/80 mmHg for diabetics), diabetes control (hemoglobin A1c<7%), hyperlipidemia control (low-density lipoprotein <100 mg/dL), medication adherence [39], social support/influence [46], physical and mental health-related quality of life [47], heart disease knowledge [40], and user evaluation of the virtual world platform (satisfaction, usability, and utility) [22,35-38].

Physical activity will be assessed by the International Physical Activity Questionnaire (IPAQ) which determines physical activity patterns (vigorous-intensity, moderate-intensity, and leisure) over the previous seven days [43]. Furthermore, free-living physical activity data will be obtained from personal activity trackers as number of steps per day [48]. All patients will undergo a symptom-limited ETT with oxygen consumption testing to assess for peak VO_2_ [52,53]. Continuous blood pressure and heart rate measurements, as well as electrocardiograms will be obtained during exercise and recovery periods. A brief dietary recall by a food frequency questionnaire will allow for diet evaluation [42]. Mayo Clinic laboratories will process and analyze all fasting blood specimens including lipid panel (total cholesterol, triglycerides, high density lipoprotein cholesterol, and low density lipoprotein cholesterol), blood glucose, and hemoglobin A1c. Physical examination measures including height, weight, body mass index, waist circumference, and blood pressure will be obtained according to standard guidelines and Mayo Clinic protocols [54-55]. The baseline questionnaires and clinical assessments will be repeated at 3, 6, and 12 months (study completion).

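### Continuous endpoints are compared on change from baseline with no baseline adjustment stated; adjusting for the baseline value already collected would be more precise

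*Protocol article*

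**What the plan says.** In the protocol article, Statistical Analysis, Quantitative Data, the analysis of clinical endpoints is given in one sentence: "we plan to calculate changes in measures by comparing differences in change from baseline to follow-up interval". It is the only between-arm comparison the section describes. The rest is descriptive, for example "For categorical variables, frequencies and proportions will be calculated", apart from a complete-case sensitivity analysis, the software and a two-sided 5% level. No baseline covariate is mentioned.

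The Phase 2 Measures section lists change in peak VO2 and several questionnaire scales among the secondary outcomes. It gives weight, blood pressure, HbA1c and LDL as thresholds. The primary outcome is a yes/no composite, with visit times given in months: "The primary outcome is a composite including improvement of at least one of the following 3 cardiac risk factors at baseline, 3, 6, and 12". The same section shows that baseline values will exist for the measures at issue: "The baseline questionnaires and clinical assessments will be repeated at 3, 6, and 12 months (study completion").

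Sample Size Estimation and Power Calculations sizes the trial on two proportions at 12 months, 45% against 74%, with 50 participants per group.

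**The concern.** A change score subtracts the whole baseline value, as if the regression of follow-up on baseline had slope 1. When the two measurements correlate at less than 1 (with equal SDs), that subtracts too much and adds baseline noise to the comparison. Adjusting for baseline lets the data set the slope.

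Two things are at stake for the continuous secondary outcomes. The first is precision, in a trial whose own limitations section names small sample size as the main weakness. The second is sensitivity to chance: if one arm happens to start higher, regression to the mean pushes its change downward, and an unadjusted change score carries that into the estimated effect.

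**Working it through.** **The plan's own figure.** Two-sided 5%, 80% power, 45% against 74%: the two-proportion formula gives 44 per group without continuity correction and 51 with it. Fisher's exact test has 80.5% power at 50 per group. The stated 50 is therefore reproduced to within rounding, and it comes from comparing proportions, not changes. It says nothing about the continuous outcomes.

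**Inputs for the continuous outcomes.** 50 evaluable patients per arm (Sample Size section); two-sided 5% level (Quantitative Data); 80% power taken as the yardstick. Assumed: equal SD at baseline and follow-up, and r, which the documents do not give and which is varied.

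**Formulas**, in units of the outcome variance at one visit:
- change score: 2(1−r)
- adjusted for baseline: 1−r²
- ratio, adjusted to change: (1−r²)/[2(1−r)] = (1+r)/2
- extra patients needed by the change score: 2/(1+r) − 1
- detectable difference in SD units: (1.960 + 0.842) × √(2v/50), with v the variance above

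| Assumed r | Change variance | Adjusted variance | Ratio | Extra patients for change score | Detectable, change | Detectable, adjusted | Adjusted power where change has 80% |
|---|---|---|---|---|---|---|---|
| 0.3 | 1.40 | 0.91 | 0.65 | 54% | 0.663 | 0.535 | 93.5% |
| 0.5 | 1.00 | 0.75 | 0.75 | 33% | 0.560 | 0.485 | 89.9% |
| 0.7 | 0.60 | 0.51 | 0.85 | 18% | 0.434 | 0.400 | 86.0% |
| 0.9 | 0.20 | 0.19 | 0.95 | 5% | 0.251 | 0.244 | 82.0% |

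These are large-sample figures. Estimating the slope takes one of 98 residual degrees of freedom, about 1%. The gain is (1−r)/2, so it exceeds that cost unless r is above about 0.98.

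**Chance imbalance.** If the arms differ at baseline by d SD, the change-score contrast is expected to move by −(1−r)d; the adjusted contrast is not expected to move. An imbalance of one standard error at 50 per arm is √(2/50) = 0.20 SD. The change-score estimate then shifts by 0.14, 0.10, 0.06 and 0.02 SD at r = 0.3, 0.5, 0.7 and 0.9. Averaged over randomisations d is zero, so this is not bias in the usual sense. It is where the extra variance comes from: (1−r²) + (1−r)² = 2(1−r).

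**The case against.** The strongest reply is that the sentence names no test or model and does not exclude baseline as a covariate. Change adjusted for baseline gives the same treatment estimate and standard error as follow-up adjusted for baseline, so the wording is compatible with the better method, and a condensed article may leave covariates to a fuller plan. This stands in part: one added phrase is enough. But the article does state a method, and read as it stands that method is a comparison of changes without adjustment.

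It is also fair that the term clinical endpoints is undefined. Baseline Visits applies the word clinical to anthropometrics, blood pressure and laboratory tests, separately from the surveys, so the sentence may not have been meant for every scale.

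Four stronger readings are tempting, and the documents do not support them.

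- **That the primary outcome is to be tested as a change score.** The sentence covers clinical endpoints, the sample size rests on two proportions, and an unnamed primary test can be left to the analysis plan.
- **That baseline adjustment would put a binary outcome right at no cost.** A yes/no outcome needs a comparison of proportions or a binary-outcome model; adjustment is optional. In a simulation of 2,000 trials with 50 per arm and one covariate of assumed strength (log odds ratio per SD of 0, 0.5, 1.0 and 1.5), unadjusted against adjusted logistic power was 84% vs 83%, 86% vs 87%, 86% vs 91% and 87% vs 94%. The odds ratio being estimated moved from 3.48 to 3.73, 4.46 and 5.70 at the same risks. Entering baseline smoking could also cause quasi-separation, because the smoking component counts "complete cessation for baseline smokers, maintained nonsmoking status for baseline nonsmokers" and one component is enough for success.
- **That the variance formula applies to weight, blood pressure, LDL and HbA1c.** Measures defines these as thresholds.
- **That baseline is likely to be a poor predictor because values may be "extracted from participant medical records from their ACS index hospitalization or follow-up medical visits".** That sentence also allows collection by standard protocols, and it concerns anthropometrics and laboratory tests. Peak VO2 comes from the treadmill test at rehabilitation intake and the scales from the baseline assessment, so it gives no ground for assuming a low r for them.

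**Conclusion.** The point holds for secondary outcomes analysed as continuous: change in peak VO2 and the self-efficacy, social support, quality-of-life and knowledge scales. For these, the comparison as stated has more variance than one adjusted for baseline. The saving from adjustment runs from 35% at r = 0.3 to 5% at r = 0.9. It assumes equal SDs and a correlation the documents do not give; if r is high, the gain is small. The change-score contrast remains unbiased over randomisations, so this is a matter of efficiency and of robustness to chance imbalance, not validity. Nothing here shows a fault in the analysis of the primary composite or in its sample size.

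**What to change.** Reword the sentence on clinical endpoints in Quantitative Data along these lines:

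- Continuous endpoints are compared between arms on the follow-up value, or equivalently the change, adjusted for the baseline value of the same measure, by ANCOVA or by a repeated-measures model of the 3-, 6- and 12-month values. The 12-month difference is reported with its confidence interval.
- The change-from-baseline sentence does not apply to the binary primary composite, which is compared as 12-month proportions, in line with the sample size calculation.

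If adjustment of the primary comparison is also wanted, prespecify the covariates, report a standardised risk difference, and check first whether baseline smoking can be entered under the composite as defined.

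The cost is wording and minor programming, with one degree of freedom per continuous endpoint. All the baseline values are already to be collected, and no patients or visits are added.

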#### Qualitative Data

Focus group interview data will be recorded, transcribed, and coded by a qualified audio typist and analyst according to a qualitative analysis approach [56]. Descriptive codes by constant comparison methods will then be merged to thematic categories and conceptual frameworks to provide insight to further the enhancement of both CR modalities [57] and barriers towards achieving ideal cardiovascular health. To ensure rigor and accuracy, separate transcription and coding will be conducted by independent analysts from the study team. All data will be processed and analyzed using the NVIVO software package.

## Discussion

### Embracing Virtual Word Technology

Telemedicine and mobile health are rapidly emerging as novel methods of the “virtualization” of healthcare delivery [58]. These technologies may serve as portals to overcome critical barriers to receipt of optimal cardiovascular care among underserved communities including the racial/ethnic minorities, the economically disadvantaged, and elderly who are disproportionately affected by CVD. Virtual world health interventions may offer a solution to this “treatment paradox” by increasing access to those who crucially need evidence-based therapies such as CR [****59]****. Further robust evidence is needed to demonstrate the effectiveness of these interventions in stimulating patient empowerment towards healthy lifestyle behavioral change. Our study will attempt to fulfill this need by assessing the feasibility and clinical effectiveness of CR delivered in a virtual world environment in comparison to standard site-based CR.

### Study Strengths and Limitations

Our study has several strengths mainly given that it is the first study, to our knowledge, assessing the use of virtual technology for CR. Furthermore, it is the only virtual world-based study focused specifically on lifestyle behavior change in patients with ischemic heart disease, the leading cause of morbidity and mortality worldwide [59]. Our study will be conducted at a designated medical center of excellence with inherent patient-centric, comprehensive, and standardized CR services. The development of the program curriculum was guided by the core components and competencies for patients and health professionals as established by the AHA and the American Association of Cardiovascular and Pulmonary Rehabilitation which could facilitate widespread adaptation and insurance reimbursement if deemed effective [49,50]. Our study will randomize study participants to a virtual world intervention as an adjunct to standard CR versus standard CR to ensure receipt of gold standard care by all participants. We will also provide all required hardware, software, and requisite computer training to both study groups. Finally, our study includes both feasibility and comparative analysis components with quantitative and qualitative assessments to ensure scientific rigor and validity.

We recognize that our study has its limitations primarily due to our small sample size, which may limit the generalizability of our results. However, this is justified as this is a feasibility and pilot study using a new method for CR delivery in cardiac patients. Another possible limitation is our provision of a laptop computer to all participants, which may not be practical or sustainable in wide-spread implementation. However, we want to ensure access to all participants and not bias our inclusion criteria by excluding those without a virtual world technology-enabled device.

### Conclusions

It is crucial that we embrace the use of novel technologies to assist cardiac patients in achieving and maintaining healthy behavioral change for secondary prevention. Virtual world technologies may fulfill this need as it has demonstrated effectiveness in improving self-efficacy for chronic disease self management even in socioeconomically disadvantaged populations [25]. We are optimistic that our proposed study of the use of virtual world-based CR will glean informative results on patient acceptability, adaptability, and ultimately empowerment toward de facto cardiovascular risk factor reduction and secondary CVD prevention.

## Abbreviations

ACS: acute coronary syndrome
AHA: American Heart Association
CAD: coronary artery disease
CR: cardiac rehabilitation
CVD: cardiovascular disease
ETT: exercise treadmill test
IPAQ: International Physical Activity Questionnaire
PCI: percutaneous coronary intervention
RCT: randomized controlled trial
VO_2_: oxygen uptake
